## Abstract

**Background:**

Pulmonary rehabilitation (PR) is a programme of exercise and education and the most effective treatment for the symptoms and disability associated with chronic obstructive pulmonary disease. However, the benefits of PR are limited by poor uptake and completion. This trial will determine whether using trained volunteer lay health workers, called “PR buddies,” improves uptake and completion of PR and is cost-effective. This trial protocol outlines the methods for evaluating effectiveness, cost-effectiveness, and acceptability.

**Methods:**

The IMPROVE trial is a pragmatic, open, cluster randomised controlled trial planned in 38 PR services across England and Wales. PR services will be randomised to either intervention arm—offering support from PR buddies to patients with chronic obstructive pulmonary disease—or to usual care as the control arm. PR staff in trial sites randomised to the intervention arm will receive training in recruiting and training PR buddies. They will deliver training to volunteers, recruited from among people who have recently completed PR in their service. The 3-day PR-buddy training programme covers communication skills, confidentiality, boundaries of the PR-buddy role and behaviour change techniques to help patients overcome obstacles to attending PR. An internal pilot will test the implementation of the trial in eight sites (four intervention sites and four in control arm). The primary outcome of the trial is the uptake and completion of PR. A process evaluation will investigate the acceptability of the intervention to patients, PR staff and the volunteer PR buddies, and intervention fidelity. We will also conduct a cost-effectiveness analysis.

**Discussion:**

Improving outcomes for chronic obstructive pulmonary disease and access to PR are priorities for the UK National Health Service (NHS) in its long-term plan. The trial hypothesis is that volunteer PR buddies, who are recruited and trained by local PR teams, are an effective and cost-effective way to improve the uptake and completion rates of PR. The trial is pragmatic, since it will test whether the intervention can be incorporated into NHS PR services. Information obtained in this trial may be used to influence policy on the use of PR buddies in PR and other similar services in the NHS.

**Trial registration:**

ISRCTN12658458. Registered on 23/01/2023.

**Supplementary Information:**

The online version contains supplementary material available at 10.1186/s13063-024-07998-x.

## Introduction

### Background and rationale

Chronic obstructive pulmonary disease (COPD) is the most common chronic lung disease caused by smoking [1]. More than a million people in the United Kingdom (UK) live with the condition, with a higher prevalence typically reported in more deprived areas [2, 3]. The symptoms of COPD include cough, breathlessness and fatigue [4]. A severe exacerbation of COPD symptoms is a key cause of attendances at Accident and Emergency departments and of hospital admissions in the UK [5]. COPD is also the third most common cause of death in England and Wales [6].

The most effective treatment for the symptoms and disability associated with COPD is pulmonary rehabilitation (PR) [7]. PR is a prescribed exercise-based treatment programme which has been identified by NICE (The National Institute for Health and Care Excellence) as one of the “five fundamentals of COPD care” [8, 9]. Structured group classes include physical exercise and information on self-management. Social interaction is a notable element in almost all services. The effectiveness of PR in improving symptoms, quality of life and exercise capacity in people living with COPD has been demonstrated conclusively in a longstanding Cochrane review now close [10]. More recently, PR has also been associated with improved survival following discharge from hospital after a COPD exacerbation [11].

Despite strong evidence demonstrating the effectiveness of PR, patients likely to benefit from it often do not receive a referral by healthcare professionals or do not join the programme. In an audit of PR services in England and Wales in 2015, the annual number of referrals of patients with COPD to 240 services was estimated to be 68,000 [12]. This equated to approximately 5% of the estimated 1.3 million people with symptomatic COPD. If patients were referred every 5 years (annual referral is desirable), the rate of referral of appropriate people with COPD would be still only 25%. In subsequent audits, 62% of the eligible patients who were referred to PR joined the programme, and 65% of those who joined the programme completed PR, an overall rate of uptake and completion of 40% [12]. The American Thoracic Society and European Respiratory Society have recommended a more collaborative approach between clinicians, patients, and funders to improve the delivery of PR within healthcare services [13].

The barriers to attending or completing PR are well understood. The reasons for poor rates of uptake include a perceived lack of benefit by patients and uncertainty about its effectiveness by those making the referral, travel issues, inconvenient timing and disruption to valued routines [14]. Reasons such as being a current smoker and having comorbidities, particularly depression, are associated with non-completion [15]. A qualitative study of patients who had recently completed PR reported that smoking was associated with feelings of unworthiness to participate in the programme [16].

Previous interventions that have sought to improve uptake and completion of PR have included computerised reminders, provision of a patient information or care manual, education for clinicians and financial incentives [17]. In 2009, Harris et al. showed in a before and after study that providing patients with a manual summarising evidence of effective care led to an 18% improvement in PR enrolment in the most socio-economically disadvantage group, compared to usual care [18]. Zwar et al. showed increased uptake of PR among patients with COPD who received care for their COPD at home by a nurse (31.1% compared to 9.6% for the control group) [19].

Lay health workers are described as “any health worker carrying out functions related to healthcare delivery, trained in some way in the context of the intervention, and having no formal professional or paraprofessional certificate or tertiary education degree” and can be involved in either paid or voluntary care [20]. Lay health workers have been used predominantly in low- and middle-income countries where their role has been to complement local health services especially where there is underfunding of conventional health services. There is evidence that using lay health workers improves uptake of clinical [21], but they are not widely used in the NHS. In the United States of America, lay health workers commonly work as patient navigators and play a range of other roles such as supporting patient self-management [22]. Adhikari et al. have published the protocol for a cluster randomised controlled trial of female volunteers in the diagnosis and management of COPD in Nepal [23]. In the context of the trial proposed here in the UK, lay health workers are an example of reverse innovation, introducing into high-income countries an innovation that was first devised in low- and middle-income countries [24].

The IMPROVE trial seeks to use lay health workers to support patients with COPD who are referred for PR to help them overcome barriers that could stop them from attending the programme. In this intervention, we train the lay health workers to use selected behaviour change techniques to overcome these barriers. In the trial, lay health workers are called “PR buddies,” a term preferred by our patient advisors. In a feasibility study of using lay health workers to improve the uptake and completion of PR, the feasibility of recruitment and training of PR-buddy volunteers was demonstrated [25]. PR buddies were successfully used in supporting patients and the fidelity of the intervention was shown [26]. Among the advantages of using PR buddies are the shared social backgrounds, and shared personal experiences of the health issue among patients and PR buddies [27].

### Objectives

The primary objective of the IMPROVE trial is to assess the effectiveness of the intervention using volunteer PR buddies trained by PR teams to improve completion of PR in patients with COPD. The working hypothesis for the trial is that PR experienced volunteer PR buddies, recruited and trained by PR staff to support COPD patients newly referred to PR, will improve uptake and completion of PR in comparison with usual care.

The secondary objectives include:To assess the intervention fidelity with respect to:The training of PR teams to set up and run a PR-buddy serviceThe recruitment and training of PR buddies by the PR teamsThe delivery of the support intervention to patients by the PR buddiesTo assess the acceptability of the intervention to trial participants, including PR staff, PR buddies and patient participants.To identify PR service, PR-buddy and patient-participant factors associated with the implementation, delivery and impact of the intervention.To conduct within-trial and longer-term cost-effectiveness analyses of the intervention compared to standard care.

The trial includes an internal pilot being conducted in eight sites, four in the intervention arm and four in the control arm. The aims of the pilot are:Testing of the PR staff training (intervention sites)Testing the feasibility of PR teams recruiting and training a group of PR buddies (intervention sites)Implementation of a PR-buddy support service to COPD patients referred for PR (intervention sites)Recruitment of patient participants (all sites)

### Trial design

IMPROVE is a prospective, open, pragmatic, cluster randomised controlled clinical trial, with an internal pilot, with clustering at site level. Sites will be PR services. The feasibility study suggested that the recruitment and training of PR buddies and the recruitment of patient participants are feasible [26]. Nonetheless, the trial is in equipoise about the effectiveness of the intervention. Trial sites will be randomised 1:1 to either PR-buddy service or to continue delivering care as usual.

## Methods: participants, interventions and outcomes

### Study setting

The IMPROVE trial will be conducted in PR centres in England and Wales. It will recruit PR services (sites) being run either by NHS staff, or by private companies contracted by the NHS. These may be community or hospital-based services. Potential sites are being identified through the list of sites participating in the National Respiratory Audit Programme and through the Clinical Research Network and regional PR networks. Each site is then contacted by a member of the IMPROVE research team. There will be an internal pilot in eight sites; the target is for the main trial to have a further 30 sites making 38 sites in total. The list of current participating sites can be obtained from the trial website: https://improvetrial.co.uk/get-involved.

### Eligibility criteria

#### Inclusion criteria

There are four groups of participants in the IMPROVE trial:(A)Trial sites(B)Individual PR staff at sites randomised to the intervention arm(C)Volunteer PR buddies (intervention sites)(D)Patient participants (all sites)

The intervention includes elements that test the efficacy of the central component of the intervention: the support of referred patients by PR buddies. It also includes elements that test the capacity for the intervention to be implemented in PR services. Because the PR staff who receive trial-specific training will deliver the training elements of the intervention to PR buddies, they will also be trial participants.

Category A—Trial sites (PR services)Provide > 15 pre-PR assessment* appointments per month (to allow for recruitment of sufficient patient participants)Collect baseline and final PR assessment data for participating patientsHave a PR completion rate ≤ 55% determined by count based on appropriate referrals received, or completion rate ≤ 65% determined by count based on patients who attend pre-PR assessmentAgree to be randomised to intervention or usual careInclude eligible patients in the invitation to be randomised for the PR-buddy intervention or usual care (researcher taking consent to be blinded to outcome of randomisation for the site)Intervention sites agree to release at least three PR staff for training; at least two of three participating staff members to be a registered healthcare professional or educated to degree level in an appropriate subjectOne or more members of the PR team to have at least 1 year’s experience in PR

*A pre-PR assessment is carried out by PR services for each referred patient to assess their suitability and record baseline data including exercise capacity. This assessment enables the exercise element of PR to be tailored to the individual.

Category B—Individual PR staff at sites randomised to the intervention armAged 18 years or aboveEmployed members of staff within the PR service at the intervention siteWilling to undertake 2½ days of training and to train, recruit, manage and support PR buddiesWilling to recruit, train and then manage and support PR buddies over a nine-month periodWilling to take part in research activities including keeping accurate records

Category C—Intervention site PR-buddy volunteersAged 18 years or aboveHave a diagnosis of COPD and have completed PR within the previous yearVolunteer for the roleUndertake training and be supervised by the PR staffWilling to support at least 6 PR patients over up to 9 monthsAble to travel independentlyWilling to use encrypted smart phones (after training) for recording conversations with supported patient participants (to enable evaluation of the intervention fidelity)

Category D—Patient participantsAged 18 years or aboveHave a diagnosis of COPDBe referred to the PR service of one of the participating sitesHave a modified Medical Research Council (mMRC) breathlessness score > 1Consent to be randomised to intervention or usual care arm of the trialConsent to receive telephone contact by PR buddy and to meet when appropriate (intervention arm sites)Consent to provide personal details to the IMPROVE research teamConsent to provide information on PR attendance to the IMPROVE research team, and to answer questionnaires on personal characteristics, impacts of PR on their health, health economic data, and data on their use of NHS services

#### Exclusion criteria

Category A—Trial sites (PR services)Unable to identify at least three members of staff who are willing to consent to participation in the trialLocal NHS health authority Research and Development (R&D) office unwilling to support the trial

Category B—Intervention site participating PR staff

Not expected to be employed in their post for the duration of PR staff training and PR-buddy training at the site.

Category C—Intervention sites PR-buddy volunteersUnable to participate for the duration of the trial at their siteUnable to travel independently to meet patient participantsUnable or unwilling to use a smart mobile phoneUnable to give valid informed consentFailed Disclosure and Barring Service (DBS) checkPregnant or breastfeedingNot deemed suitable to work with patient participants, as assessed by a Health Care Professional

Category D—Patient participantsHave poorly controlled angina on minimal exertion (defined as history of heart pain when walking on level ground)Have had a myocardial infarction in the 6 weeks prior to being approached to give consentHave breathlessness as a result of cardiac diseaseHave uncontrolled hypertensionHave any medical problem that severely restricts exercise or compliance with the programmeUnable to give valid informed consentPregnant or breastfeeding

### Consenting participants

PR-staff research participants will be in the intervention arm of the trial. They will give written informed consent after the site has been randomised. Sufficient time will be allowed for the invited staff to read the participant information sheet and to have the opportunity to ask questions. Consent will be taken by a member of the IMPROVE research team on a video call. Volunteers who would like to become PR buddies will give written informed consent in-person during the first day of the PR buddies’ training having previously been sent the participant information sheet. Consent will be taken by a trained member of PR staff or a member of the IMPROVE research team after the PR buddy has had a chance to ask questions.

Patient participants will give their consent to local National Health Service (NHS) research delivery staff or Clinical Research Network (CRN) staff. Patient participant consent may be taken in-person or remotely through a phone or video call, depending on individual preference. All potential participants will be sent the patient information sheet and the consent form in advance of consent meetings. After having an opportunity to ask questions, if the patient consents they will sign and date the consent form. In in-person consent interviews, the research staff member will countersign and date the form and give a copy to the patient. Where consent is given remotely, two methods may be used. The patient may sign and date the consent form and send it to the research staff member who will then sign and date it and send a copy to the patient. The alternative method is for the research staff member to audio-record the patient giving verbal consent by telephone and to securely store the recording. The research staff member should sign the consent form and send a copy to the patient. [Communication from the Preston Research Ethics Committee, 19 April 2023].

As part of the trial process evaluation, some patient participants and some PR staff will be invited to a qualitative interview, and some PR buddies will be invited to participate in focus groups to provide feedback on their experience of participating in the trial. Participants consenting to give one-to-one interviews or to participate in a focus group will additionally consent to these interactions being recorded and transcribed. Consent to participate in a qualitative interview or focus group will be taken at the same time as written informed consent for participation in the trial as described above.

This trial does not involve the use of any biological specimens.

## Intervention

Randomisation will be at the PR-service level. Rates for completion of PR for patient participants who receive PR-buddy support in services in the intervention arm will be compared to those for patient participants in PR services randomised to offer care as usual. Randomisation at the level of sites is essential to prevent contamination of patient participants not receiving the PR-buddy intervention by those who are receiving it or who have received it. For this reason, the comparison will be between sites and not between individual patient participants. Recruitment of patient participants will be identical in both arms of the trial. Patient participants will not be aware of the outcome of the PR service randomisation at the time of recruitment. The site target for recruitment of patient participants, at least 36, will be the same for all sites.

The IMPROVE PR-buddy intervention has five elements: PR-staff training, PR-buddy recruitment, PR-buddy training, patient-participant support by the PR buddies, and PR-buddy management and support by the PR staff. A ‘train-the trainer’ approach will be used, whereby designated PR staff in services in the intervention arm of the trial will be trained in the setting up and running of a PR-buddy service. Using this model moves the burden of training multiple groups of PR buddies from the IMPROVE research team to individual PR services. This will help to provide a more realistic assessment of the intervention as it would be implemented in ‘real-world’ practice and will also facilitate implementation across the NHS if the trial outcome is positive.

The PR-buddy training will be informed by the COM-B model and include selected behaviour change techniques. The COM-B model for behaviour change proposes that there are 3 components to any behaviour: capability (C), opportunity (O), and motivation (M) [28–30]. PR buddies sharing their own positive experiences of PR with patient participants will be a central element of the PR-buddy intervention. Manuals for the training for PR staff and the training of PR buddies will be freely available for services in the NHS only after completion of the trial.

The intervention includes the following steps:
*Step 1*: Training will be delivered to at least three PR staff members from each intervention site by the IMPROVE team. The 2.5 days PR staff training comprises a half day self-directed learning session, 1 day “remote live”; by which we mean that the participants will attend the training at the same time, but it will be delivered remotely using Microsoft Teams. The final day will be in-person training.
*Step 2*: PR staff will recruit volunteer PR buddies by writing to people with COPD who completed PR in their service in the last year. Patients completing their end of PR assessment will also be informed about the IMPROVE trial. PR staff will screen interested volunteers by phone. Selected volunteers will be asked to complete an application form and will be invited for an in-person interview by PR staff. At interview, the suitability of volunteers for the role will be checked. Candidates will either be offered a place on the PR-buddy training course or signposted to other volunteering opportunities.
*Step 3*: PR staff will train the PR buddies in supporting patients who are referred for PR. The focus will be on training PR buddies to identify and work with patients to resolve potential barriers to attending PR including the PR buddies sharing their own positive experiences of PR with patient participants. Communication skills, confidentiality and boundaries of the role will also be included. The training will be delivered in-person once a week for 3 weeks.
*Step 4*: PR staff will allocate PR buddies to patient participants, and the PR buddies will make initial contact by phone. PR buddies and supported patients will be encouraged to also meet in person if both agree. Mean number of encounters (telephone and face to face) is expected to be about six [25].
*Step 5*: PR buddies will have monthly group support meetings facilitated by the trained PR staff. At these meetings, the PR buddies will have opportunities to share experiences, recap elements of the PR-buddy training and allow PR staff to ensure that the PR buddies’ workload is acceptable and that the contact they are having with their patient participants is sufficient.

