### Plans to promote participant retention and complete follow-up

PR-staff retention will be promoted at each site by having a designated link researcher from the IMPROVE team. These researchers will attend 2 out of the 3 days of PR-buddy training to assist with completion of trial-related paperwork, such as consenting PR buddies and completion of volunteer agreements. The link researcher will visit intervention sites monthly to collect recorded phone data and to link with the PR team regarding any other research management issues.

PR buddies will attend monthly meetings at which they will be offered ongoing support from PR staff. The support will include checking on interactions with patient participants, identifying any patient participants who the PR buddy is having difficulty supporting and providing remedies, sharing experience and solutions to common problems. PR buddies who withdraw while they are supporting patients will be asked to stay in contact with these patients until they end of their PR. If they are not able to do this, then the patients will be reassigned to another PR buddy by PR staff. Patient participants who wish to withdraw will be invited to complete the follow-up data collection questionnaires before leaving the trial.

Any PR staff or PR buddies who choose not to or are unable to continue until the end of the trial will be asked to participate in a qualitative interview as part of the process evaluation. Data that are collected before patient participants withdraw will be retained for analysis.

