### Statistical methods for primary and secondary outcomes

Except for enrolled clusters/patients who are found to be ineligible or who withdraw consent at baseline visit and so never receive any treatment, and for whom no data are available, main analyses will be on an intention to treat basis to reflect the randomisation process.

Chi square test adjusting for cluster effect will be used to compare the rates of completion of PR in the two trial arms. Further, a mixed effect logistic model will be used in a sensitivity analysis to adjust for potential confounders, including age, gender and site size. In addition, adjustment for cluster-level variables will be applied for selected variables including site (cluster) size.

The estimates for primary outcome will be presented as odds ratios with 95% confidence intervals for the effect of intervention. Statistical significance will be determined at 5% level using a two-sided test throughout.

A generalised linear mixed model with linear link function will be used to analyse secondary continuous outcome measures. Working correlation matrices will be unstructured, which is not unduly restrictive given that measurements are only taken at three time points. The sandwich estimator of covariance matrix will be used to obtain appropriate (consistent) estimates of precision. Analysis of secondary endpoints will be done at the individual level.

The study has no interim analysis planned.

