### Methods for additional analyses

Subgroup analyses of the principal outcome measure, completion of pulmonary rehabilitation, are planned to assess the impact of the following: the number of pulmonary rehabilitation sessions attended by patient participants; interval between offer of appointment for pre-PR assessment and first PR class; type of pulmonary rehabilitation programme (rolling or cohort).

Multiple imputation methods will be used, incorporating any available information from the baseline assessment and explanatory variables to impute missing primary or secondary outcome measures. Sensitivity analyses to assess the robustness of the results to various assumptions regarding missing data, or participants lost to follow-up, will be conducted.

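### The Intervention section limits the intervention group to patients who receive buddy support, against the stated intention-to-treat analysis; the exception to that analysis also needs tightening

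*Protocol article*

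**What the plan says.** Three parts of the protocol article bear on who is analysed.

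- **Intervention.** "Rates for completion of PR for patient participants who receive PR-buddy support in services in the intervention arm will be compared" with the rates for patient participants in services randomised to usual care. Shortly afterwards: "the comparison will be between sites and not between individual patient participants".
- **Outcomes.** The primary outcome is completion by each individual patient participant, summarised per site. No condition on receiving support is attached.
- **Statistical methods for primary and secondary outcomes.** "main analyses will be on an intention to treat basis to reflect the randomisation process". An exception is made for enrolled clusters or patients "found to be ineligible or who withdraw consent at baseline visit and so never receive any treatment, and for whom no data are available".

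Two further statements limit how far patients can fall out. Under the plans for retention, "Data that are collected before patient participants withdraw will be retained for analysis". Under Methods for additional analyses, multiple imputation is to be used "to impute missing primary or secondary outcome measures".

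**The concern.** Read as written, the sentence in the Intervention section selects one arm on an event after randomisation and leaves the other arm whole. Randomisation does not protect such a comparison. Patients who decline a buddy, or whom a buddy cannot reach, may well be poorer completers, and removing them would raise the intervention rate without any effect of the intervention.

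Some non-receipt is foreseeable. Support depends on buddies being recruited, trained, allocated and then making contact by phone. The section on discontinuing or modifying the intervention provides for patients and buddies withdrawing from each other. Patients also consent without knowing their site's allocation.

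The exception to intention to treat raises a smaller issue. It allows removal for ineligibility after allocation, and three features could make it work differently in the two arms:

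- One Category D inclusion criterion, consent to contact by a buddy, is labelled for intervention sites only. A refusal could be recorded as ineligibility in that arm alone.
- Suitability is assessed at the pre-PR assessment by PR services, whose staff know the allocation. One patient exclusion criterion, a medical problem severely restricting exercise or compliance, calls for judgement.
- The treatment that an excluded patient must never have received is not defined. Control patients have no buddy support to receive. If PR itself is meant, never receiving it is a failure on the primary outcome.

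**Working it through.** **The plan's own figure.** Inputs from Sample size: 40% against 56%, 90% power, ICC 0.056, 30 patients per site. The two-sided 5% level is in the statistical methods section.

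- Patients per arm before clustering (pooled variance, no continuity correction): [1.96 × √(2 × 0.48 × 0.52) + 1.2816 × √(0.40 × 0.60 + 0.56 × 0.44)]² / 0.16² = 202.8, so 203.
- Design effect: 1 + (30 − 1) × 0.056 = 2.624.
- Sites per arm: 203 × 2.624 / 30 = 17.8, so 18.
- For 32% against 48%: 195 × 2.624 / 30 = 17.1, so 18.

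The stated 18 per arm is reproduced. It does not depend on the disputed sentence.

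**Bias if only recipients were analysed.** Let p be completion in both arms (no true effect), f the share of intervention patients who never receive support, and q completion among them. Values of f and q are assumptions; the documents give neither.

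- Rate among recipients: r = (p − f × q) / (1 − f).
- Bias: r − p = f × (p − q) / (1 − f). It is positive when q is below p, zero when q equals p, and negative when q is above p.

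Rejection probability is from a normal two-sided 5% test with 18 sites per arm. The control arm has 30 patients per site and the intervention arm 30 × (1 − f). The variance of the difference is p(1 − p) × 2.624 / 540 + r(1 − r) × [1 + (30(1 − f) − 1) × 0.056] / [540(1 − f)].

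| p | f | q | r | Bias (points) | Odds ratio | Rejection |
|---|---|---|---|---|---|---|
| 40% | 10% | 20% | 0.38/0.90 = 42.2% | 2.2 | 1.10 | 7.4% |
| 40% | 10% | 10% | 0.39/0.90 = 43.3% | 3.3 | 1.15 | 10.4% |
| 40% | 20% | 20% | 0.36/0.80 = 45.0% | 5.0 | 1.23 | 17.1% |
| 40% | 20% | 10% | 0.38/0.80 = 47.5% | 7.5 | 1.36 | 32.4% |
| 32% | 10% | 20% | 0.30/0.90 = 33.3% | 1.3 | 1.06 | 5.9% |
| 32% | 20% | 10% | 0.30/0.80 = 37.5% | 5.5 | 1.27 | 20.9% |

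Outside that range at p = 40%: f = 5% with q = 0 gives 42.1% and 7.2% rejection; f = 20% with q = 0 gives 50.0% and 51.8%.

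**Under intention to treat.** The non-recipients stay in the denominator. In the fourth row, 0.20 × 0.10 + 0.80 × 0.475 = 0.02 + 0.38 = 0.40, so the bias is zero.

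**Reach of the exception.** It joins three conditions: ineligible or consent withdrawn at the baseline visit; for that reason never treated; and no data available. An eligible, consented patient who never attends, or never gets a buddy, fails the first condition and stays in as a non-completer. The exception names no arm. What it leaves open is which ineligibility criteria count, who judges them and with what knowledge of allocation.

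**The case against.** The strongest reply is that the Intervention section is not the analysis plan. It explains why sites are randomised, and it says that the comparison is between sites. The statistical methods section commits to intention to treat, the outcome is defined for every patient participant, and the Abstract describes the intervention arm as offering support. On this view the sentence is loose wording, and detailed analysis sets belong to the SAP, which is not shown.

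Much of this stands. The documents do not plan an as-treated primary analysis, and a reader who infers one goes too far. The between-sites sentence does not settle the matter, however: a site proportion can be computed with recipients alone in the denominator. Two published statements of the same comparison differ, and a SAP could be written from either.

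Two other stronger readings also fail.

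- A reader might infer that the exception drops anyone found ineligible, or anyone who never starts PR. It does not, because it also requires that no data be available, and mere non-attendance is not ineligibility.
- A reader might infer that the site criterion of three willing staff can be failed only after randomisation and only in the intervention arm, since of staff participants it is said that "They will give written informed consent after the site has been randomised". But the criterion concerns identifying willing staff and is listed for all sites. The Recruitment section uses the expression of interest form and information meeting to check site eligibility, and randomises afterwards. Nothing says that an intervention site that fails to deliver the buddy service is removed.

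**Conclusion.** The contradiction is real and concerns the population of the primary comparison in an open trial, so it should be resolved. Its consequence is conditional: bias arises only if the Intervention wording overrides the intention-to-treat statement. In that case, with no true effect and 40% completion, the false gain is 2.2 to 7.5 points and rejection is 7% to 32% instead of 5%. This rests on the assumed 10-20% non-receipt with 10-20% completion among non-recipients. If intention to treat is followed, this bias is zero.

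The concern about the exception is narrower and is not quantified here. Its conditions already keep it small, but it permits removal after allocation on criteria that are not plainly the same in both arms, nor plainly judged blind.

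**What to change.** - **Intervention section.** State that completion is compared between all consented patient participants in services randomised to the intervention and all consented patient participants in services randomised to usual care, whether or not a buddy made contact. Any analysis by receipt of support should be labelled supplementary (for example a complier-average effect).
- **Statistical methods section.** Keep the condition that no data are available. Limit exclusions for ineligibility to criteria that are identical in both arms and judged blind to allocation. State that declining a buddy, not receiving one, or not attending PR is never a ground for exclusion. Report exclusions of sites and patients, with reasons, by arm.
- **SAP.** Carry over the same definitions.

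The cost is wording. The sample size stays at 18 sites per arm, 38 in total with the allowance for site dropout. The estimate may be slightly less favourable than one based on recipients only.
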